#### Data management plan

2.6.3

The study will utilize REDCap (Research Electronic Data Capture), a free, web-based application designed to support data capture for research studies. The database will be hosted on secure, password-protected servers. The database is fully HIPAA compliant and provides audit capabilities. All study data will be inputted into REDCap by study staff and the platform provides automated export procedures for seamless data downloads to Excel and common statistical packages.

## Anticipated results

3

### Expected outcome

3.1

The primary endpoint of this study is insulin sensitivity which will be evaluated by the hyperinsulinemic euglycemic clamp and estimated by the HOMA-IR. The secondary endpoints demonstrated in **Table 6** are glucose and c-peptide measurements performed after the modified mixed meal tolerance test, liver fat quantification, total body fat mass and body composition evaluated by DEXA scan, serum levels of fasting glucose, insulin, c-peptide, liver function tests, fasting lipid panel, hsCRP, circulating inflammatory cytokines (TNF-a, IL1-B, IL-6), FABP4, glucagon, POA, free fatty acids, glycerol, adiponectin, and leptin. We expect POA compared to placebo to improve insulin sensitivity, glucose tolerance, hepatosteatosis, whole-body fat mass, serum profile of lipids, and inflammatory markers. Additionally, we anticipate a higher therapeutic impact of POA in women compared to men.

**Table 6 T6:** Outcomes.

**Primary Endpoint**	Insulin sensitivity, evaluated by hyperinsulinemic euglycemic clamp (gold standard test), and estimated by the HOMA-IR
**Secondary Endpoints**	Liver fat quantification (evaluated by liver MRI-PDFF)
	Modified mixed meal tolerance test (standardized evening mixed meal response)
	Total body fat mass and body composition (will be evaluated by DEXA scan)
	Serum; fasting glucose, insulin, C-peptide, LFTs, fasting lipid panel, hsCRP, circulating inflammatory cytokines (TNFa, IL1-B, IL6), FABP4, glucagon, POA, free fatty acids, glycerol, adiponectin, leptin, and cortisol.

### Benefits

3.2

Successful completion of the study will lead to a better understanding of the effects of POA on glucose and lipid metabolism. Understanding the effects of POA on insulin sensitivity and lipogenesis has the potential for a profound public health impact in the fight against obesity and type 2 diabetes. Possible positive results of this study might create a new dietary approach to prevent and/or treat diabetes and related complications such as fatty liver disease. High-quality unsaturated fatty acids (such as omega-3) have been shown to improve dyslipidemia and improved the lives of people with cardiovascular disease (72). Testing the effect of omega-7 fatty acids like POA will increase the understanding of how high-quality fatty acids could be beneficial for insulin resistance and prediabetes in addition to dyslipidemia. There will be no direct benefit to the subject for taking part in this study.

### Pitfalls and alternative approaches

3.3

This is an 8-week clinical trial, and the duration might not be sufficient to observe the beneficial effects of POA on insulin sensitivity. Because other studies demonstrate the effects of POA on metabolism after 1 month, we decided to limit the study timeframe to 8 weeks to make sure patient compliance is established (27, 47). The study is powered for the insulin sensitivity measured with the gold standard method of the hyperinsulinemic-euglycemic clamp. Therefore, 40 participants may not be adequate to exhibit statistically significant differences in secondary endpoints being liver fat mass, total body fat mass, body fat composition, glucose and c-peptide levels post-mixed meal, serum glucose, insulin, c-peptide, liver function tests, fasting lipid panel, hs-CRP, circulating inflammatory cytokines (TNF-a, IL1-B, IL-6), FABP4, glucagon, POA, free fatty acids, glycerol, adiponectin, leptin measurements. Additional studies designed to focus on secondary endpoints might be necessary to show significant effects. We aim to select participants who has insulin resistance via using criteria identifies individuals with overweight-obesity and prediabetes. However, we might still get participants with high insulin sensitivity, where there might not be enough therapeutic window to improve. In that case, we might need to add more strict inclusion and/or exclusion criteria or randomize potential insulin sensitive participants equally to treatment arms.

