#### Sample size and power

2.6.2

The study is powered only for the primary endpoint, insulin sensitivity. We expect a mean insulin sensitivity-M value (measured as steady state clamp glucose infusion rate) of approximately 7.5 ± 1.7 mg/kg/min with placebo, based on previous clamp studies^30^. Based on previous human studies, we expect to see at least a 20% difference between placebo vs. POA treatments. A sample size of 40 subjects with complete data will provide greater than 80% power for these assumptions. We will perform stratified randomization based on subjects’ BMI (<30>), and gender for homogenous treatment groups. 3:2 POA vs placebo assignment will allow us to achieve this randomization goal. We were also implementing oral glucose tolerance test results for the additional stratification of the randomization, however additional invasive testing before starting the trial period caused scheduling conflicts and compliance problems. Hence, we have discontinued OGTT for the stratification criteria.

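### The fallback of randomising insulin-sensitive participants equally, if it means 1:1, conflicts with the 3:2 scheme and would tie allocation to the baseline level of the primary outcome

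*Protocol article*

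**What the plan says.** Protocol article, section 2.6.2 (Sample size and power), sets the allocation: "We will perform stratified randomization based on subjects’ BMI (<30>), and gender for homogenous treatment groups", followed by "3:2 POA vs placebo assignment will allow us to achieve this randomization goal". Insulin sensitivity is not a stratification factor. A glycaemic factor was once used, but for scheduling and compliance reasons "we have discontinued OGTT for the stratification criteria".

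Section 3.3 (Pitfalls and alternative approaches) considers that some participants may turn out to be insulin sensitive, with little room to improve. It continues: "In that case, we might need to add more strict inclusion and/or exclusion criteria or randomize potential insulin sensitive participants equally to treatment arms". It does not define who counts as potentially insulin sensitive, what triggers the change or who decides, and it does not relate *equally* to 3:2.

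Section 2.6.1 (Statistical methods) names a paired t-test and a Wilcoxon test on before and after values, plus a regression. The covariates given as examples are age, sex, sleep and BMI. Neither week-0 M nor an allocation stratum is among them.

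**The concern.** Randomisation protects the comparison of arms when every participant has the same chance of POA, or when the analysis accounts for the groups in which that chance differs. On the 1:1 reading neither is secured by the text. Insulin-sensitive participants would be over-represented on placebo by design, and the characteristic involved is the baseline level of the primary endpoint.

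The consequence depends on the comparison. On week-8 values, placebo would look better because it holds more people with high M. On change from baseline, POA would look better: high baseline values tend to fall back on repeat measurement, and more of them would be on placebo. If POA works mainly in insulin-resistant people, as section 3.3 suggests, the change comparison moves a little further towards POA. The study hypothesis concerns POA against placebo, so the between-arm comparison is the one that matters.

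**Working it through.** **Planning figures (section 2.6.2).** M is "approximately 7.5 ± 1.7 mg/kg/min with placebo", and "we expect to see at least a 20% difference between placebo vs. POA treatments". The target is 0.20 × 7.5 = 1.5 mg/kg/min. With 40 completers at 3:2 (24 and 16), the standard error is 1.7 × √(1/24 + 1/16) = 0.549 and 1.5/0.549 = 2.73. Two-sided power at 5% is Φ(2.73 − 1.96), about 78% (75.9% with the exact t); one-sided it is about 86% (85.1%). The stated power above 80% is therefore nearly or fully reproduced, depending on sidedness, which the article does not give. This does not bear on the present point; the 1.5 and 1.7 are used below.

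**Assumptions not in the document.** The share insulin sensitive, q, is 10 to 40%. The pre-post correlation, ρ, is 0.5 to 0.9. Baseline M is normal with SD 1.7, and the sensitive group is the top q of that distribution.

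**Step 1, make-up of the arms (1:1 for sensitive, 3:2 for the rest).**
- Share sensitive in POA = 0.5q / [0.5q + 0.6(1 − q)]
- Share sensitive in placebo = 0.5q / [0.5q + 0.4(1 − q)]

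**Step 2, gap in mean M** between the top q and the rest = 1.7 × φ(z) / [q(1 − q)], where z cuts off the top q and φ is the normal density.

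**Step 3, baseline difference between arms**, D = (difference in shares) × gap.

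| q | POA | Placebo | Difference | Gap | D |
|---|---|---|---|---|---|
| 10% | 0.05/0.59 = 8.5% | 0.05/0.41 = 12.2% | 3.7 points | 3.31 | 0.123 |
| 25% | 0.125/0.575 = 21.7% | 0.125/0.425 = 29.4% | 7.7 points | 2.88 | 0.221 |
| 40% | 0.20/0.56 = 35.7% | 0.20/0.44 = 45.5% | 9.7 points | 2.74 | 0.267 |

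**Step 4, distortion when POA has no effect.**
- Week-8 values: −ρD, from −0.5 × 0.123 = −0.06 to −0.9 × 0.267 = −0.24. As a share of 1.5, that is 4 to 16%, against POA.
- Change from baseline: +(1 − ρ)D, from 0.1 × 0.123 = 0.012 to 0.5 × 0.267 = 0.13, towards POA.

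**Step 5, simulation** (N = 40, 40,000 runs per scenario; 4,000 for the adjusted model).
- Week-8 values: −0.062 to −0.243, type I error 5.2 to 7.1%.
- Change: +0.015 to +0.134 (1 to 9% of 1.5), type I error 5.0 to 5.7%.
- Mixed allocation with adjustment for baseline M: at most 0.01, type I error 4.3 to 5.6%, which is nominal within simulation noise.
- 3:2 throughout, unadjusted (q = 25%, ρ = 0.7): 0.001 on week-8 values and 0.002 on change, type I error 5.0%.

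**Step 6, unequal response.** If sensitive participants gain 0 and the others 1.5 (q = 25%, ρ = 0.7), the change comparison gives 1.24 under mixed allocation and 1.13 under 3:2 throughout. With adjustment for baseline M the two are 1.14 and 1.14.

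**The case against.** The case against has real weight.

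- **The fallback is tentative.** It is one of two options in a section on pitfalls. The adopted scheme is 3:2, and nothing says the fallback was or will be used. This stands, so the finding concerns what would follow from using it.
- ***Equally* may mean balanced.** Spreading sensitive participants evenly over the arms at 3:2 would suit the stated aim of homogeneous groups and would cause no bias. This is possible, but 1:1 is the plainer sense of the words, and a pharmacy needs an unambiguous instruction.
- **The named primary test is paired.** Within-person differences cancel baseline level, and a within-arm paired test is not affected by unequal levels between arms. This stands, but such a test does not compare POA with placebo. In a comparison of changes, regression to the mean remains, and it is small.
- **The covariate list is open, and an analysis plan may exist.** This also stands: adjustment for baseline M all but removes the distortion under the null.

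A reader might infer that the primary comparison is biased as planned. The four points above rule that out. A reader might also assume that sensitive participants have M higher by 3 to 4 mg/kg/min and arrive at a bias of 17 to 27% of the target. The protocol's own SD argues against this. Two groups with shares p and 1 − p must satisfy p(1 − p) × gap² ≤ 1.7². The gap therefore cannot exceed 1.7/√0.21 = 3.71 at p = 30% or 1.7/√0.25 = 3.40 at p = 50%. Under a normal distribution, the top 30% exceed the rest by about 2.8, which gives about 0.086 × 2.8 = 0.24, or 16%. Nor does dropping the OGTT suggest outcome-driven changes to randomisation, since the article gives practical reasons for it.

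**Conclusion.** The point holds as a conditional one. Read as 1:1, the fallback in section 3.3 contradicts the 3:2 ratio in section 2.6.2 and makes allocation depend on baseline insulin sensitivity, while the analysis named in section 2.6.1 has no term that accounts for it. If it were used, an unadjusted between-arm comparison would be distorted by the 4 to 16% (week-8 values) or 1 to 9% (change) shown above, in opposite directions. The effect on type I error is modest for week-8 values and slight for change.

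The sizes rest on the assumed share, correlation and normal distribution, and on sensitive participants being identified from M itself. A cruder screening measure would separate the groups less well and give smaller figures. The distortion is worth removing mainly because that is easy and because the wording concerns randomisation itself.

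**What to change.** 1. In section 3.3, remove the option of equal randomisation. If balance on insulin sensitivity is wanted, offer instead a screening HOMA-IR stratum with a stated cut-off and the same 3:2 ratio in every stratum.
2. Compare the arms with a model for week-8 M adjusted for week-0 M. If any participants have been randomised at another ratio, add a term for that stratum or period.
3. State that any change to eligibility or strata is decided on pooled baseline data by people blind to arm, and record its date.

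**Cost.** This needs a wording change and an instruction to the research pharmacy. HOMA-IR is already an eligibility criterion, and week-0 M is already measured. The real price is one more stratum in a 40-person trial: BMI and sex make four cells, a third two-level factor makes eight, and 40/8 = 5 participants per cell on average is a single 3:2 block. If that is too thin, omit the stratum and rely on 3:2 throughout with adjustment for week-0 M.

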## Discussion

4

Following the accumulation of evidence from animal studies, several positive association studies have demonstrated the correlation of POA with decreased insulin resistance and diabetes incidence. A study with 100 Caucasian non-diabetic, overweight volunteers with first-degree type 2 diabetic relatives undergoing 9 months of lifestyle intervention demonstrates that circulating POA is a strong and independent determinant of insulin sensitivity measured by hyperinsulinemic-euglycemic clamp tests, implying its critical role in the pathophysiology of insulin resistance in humans (46). Another study performed with non-diabetic participants has shown that plasma POA is an independent determinant of glucose tolerance, insulin sensitivity, and beta cell function in non-diabetics. This underscores POA’s key role in protecting systemic glucose metabolism from the detrimental effects of excess NEFA and adiposity (44). After the improvements in glucose metabolism in preclinical models and association studies, an extensive longitudinal study was performed. Data from 16 prospective studies with 63,682 participants without known diabetes at baseline and 15,180 participants who developed cases of type 2 diabetes over the average of 9 years and over up to 20 years of follow-up were analyzed. POA was measured as a biomarker of dairy fat consumption. This large meta-analysis shows that higher POA levels are associated with a lower risk of developing Type 2 diabetes mellitus (61). Yet, some association studies claimed a positive correlation between obesity and POA and interpreted it as a negative impact (73–85). Despite the claims of others, we think that the increased levels of POA are due to its role as a rescue mechanism of the body against gluco-lipotoxicity. *In vitro* experiments done in human islet cells supports this idea by demonstrating that POA ameliorates the detrimental effects of palmitic acid by lowering high glucose-induced apoptosis of beta cells (7). Several human interventional studies focusing on the effects of a POA-enriched diet on dyslipidemia have been carried out. For instance, 0.75 ml/day sea buckthorn seed oil (4.89% POA) supplementation for 30 days prompted a 27% decrease in LDL cholesterol in hypertensive individuals (86). Furthermore, the administration of 15% of daily caloric intake with macadamia nuts (high in POA) for 4 weeks resulted in a 5.3% decrease in LDL cholesterol, a 3% reduction of total cholesterol, and a 7.9% increase in HDL cholesterol levels in hypercholesterolemic men (48). Additionally, a study comparing a Macadamia nut rich diet (42.5-gram POA/day) with an Average American Diet showed an 8.9% decrease in LDL cholesterol and a 9.4% decrease in total cholesterol (50). However, some of the studies failed to show beneficial effects. Perhaps this is because these studies administered POA supplements that contained a significant amount of palmitic acid which can mask the beneficial effects of POA. In summary, association studies could be misleading both positive and negative ways according to many confounders, which is hard to control. Thus, there is a critical unmet need to assess the causal effects of POA directly and blindly (un-biased) on human glucose and lipid metabolism.

While designing translational studies, one of the most important aspects is safety. Unsaturated fat, namely POA, has beneficial effects on glucose metabolism, whereas the same amount of saturated fat, namely palmitic acid, is detrimental (22, 44). This concept has been proven by investigating the dietary habits of Greenland Eskimos in the 1970s. Their diet consisted of 55% fat enriched with POA (3 times higher than a Western diet, an average of 6.54 grams/day), which surprisingly resulted in significant protection from diabetes, dyslipidemia, and coronary heart disease as compared to Eskimos living in Denmark, who were consuming a Western diet (87, 88). POA is the second most abundant monounsaturated fatty acid within the standard American diet (89). The average Western diet consists of approximately 2 grams of POA (90). Human intervention studies have documented the consumption of up to 15.3 g of POA/day for the duration of up to four weeks, with no serious adverse effects reported (48). According to an expert panel, 5 g POA/d (as 10 g of either Provinal® EE or TG) for the average user and 10 g POA/d (as 20 g of either Provinal® EE or TG) for a 90th percentile user is Generally Recognized as Safe (GRAS) (91). 1512 mg of pure palmitoleic acid will be given to the treatment arm in our study. The available evidence suggests that consumption of POA within the specified intake levels does not result in any significant adverse effects.

To date, there are no clinical trials that have assessed the impact of supplementation with pure POA versus placebo on glucose tolerance and insulin resistance in humans. The proposed randomized, placebo-controlled study will address this gap in knowledge, and give us an opportunity to possibly translate our basic science discovery to humans. Here we hypothesize that we can mimic the rescue mechanism of adipose tissue against obesity by supplementing high dose POA exogenously, which will improve whole-body insulin sensitivity and ameliorate hepatosteatosis.

## Ethics statement

The studies involving humans were approved by Mass General Brigham institutional review board. The studies were conducted in accordance with the local legislation and institutional requirements. The participants provided their written informed consent to participate in this study.
